## Research objectives

Aim 1: Evaluate the implementation of OTCH at 12 months and 24 months in a cluster-RCT.Compare OTCH vs Usual FEP care on service and implementation outcomes.Examine whether factors at community-, provider-, and participant-level moderate service and implementation outcomes of OTCH vs Usual FEP care.

Aim 2: Evaluate the effectiveness of OTCH vs Usual FEP Care at 12 months and 24 months.Compare the effectiveness of OTCH vs Usual FEP care on symptoms, functioning, and recovery orientation.Test both Service and Implementation Outcomes at 12 months as mediators of the effectiveness of OTCH vs. Usual FEP care at 24 months.

Aim 3: Estimate the cost of delivering OTCH vs Usual FEP care over a 24-month period.

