The second phase constitutes the bulk of the 2-year program. Once a strong relationship has been established with the participant and family and individualized goals have been defined, team members will provide interventions focused on helping individuals achieve their goals and promote their recovery as well as deliver core sessions providing psychoeducation about FEP, its course, treatment and information to support recovery and resilience to participants and family members. During this time period, meetings with the PC, Prescriber/Nurse, and other team members will continue to happen as frequently as needed depending on the interventions being delivered and participant/family preferences. As participants start reaching goals and becoming more involved in community and school/work activities it is typical that meetings with team members decrease in frequency. The final phase begins six months prior to discharge from the program and is focused on understanding the participant’s achievements, and the identification of future needs to determine connection to long-term services.

The intervention is offered in a flexible manner, responsive to the needs and preferences of each participant which helps to limit disengagement from services. If participants decide that they do not want to take engage in any part of the model, the services offered will be modified to meet this request. Participants should not receive other concomitant psychiatric treatment during the time that they are receiving care from the OTCH team because the interventions provided by the team are comprehensive and should treat primary psychosis and other psychiatric comorbidities. Criteria for discontinuation of the intervention would be based on clinical judgment indicating that (1) the diagnostic presentation has changed, and the individual has a different psychiatric disorder requiring different services or (2) the worsening of symptoms requiring a different level of care such as inpatient hospitalization. Furthermore, if a participant decides that they no longer want to receive services from the OTCH team, an appropriate referral and linkage will be made either to another service within the community mental health center or to another mental health service provider (Table 2).

**Table 2 Tab2:** Typical activities of each phase of the intervention

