		Providers and participants	The *Recovery Self-Assessment (RSA)* [24] provider and patient versions is a 32-item, self-administered rating scale that focuses on perceptions of recovery principles and overall quality of services. It captures both providers’ and patients’ perceptions that a specific recovery-oriented intervention, in this case OTCH, is agreeable, palatable or satisfactory. Each item is rated on a 5-point scale (1 = Strongly Disagree; 5 = Strongly agree). Higher scores indicating greater quality care. Range: 32–160 points.	Baseline, 12, 24 months	15 min
		Providers and partcipants	Ten ad-hoc questions regarding receipt of services that are central to OTCH including supported employment-education, family intervention/support, psychosocial interventions, and personal strenghts and resiliency training	Baseline, 12, 24 months	3 min
Service outcomes	Patient-centeredness	Participants	The *Youth Services Survey (YSS)* [25] is a scale that assesses perceptions about accessibility, quality, and impact of mental health service over a period of time. Only the first 15 items will be used in this study. Each item is rated on a 5-point scale from 1= “Strongly disagree” to 5 = “Strongly agree” (Range: 15–75 points).	Baseline, 12, 24 months	10 min
	Medication adherence	Participants	Measured by the *Brief Adherence Rating Scale (BARS)* [26] It consists of 4 items: 3 questions and an overall visual analog rating scale to assess the percentage of antipsychotic medication doses taken by the user in the past month (0–100%).	Baseline, 12, 24 months	5 min
	Retention	Participants	Time remaining in treatment will be estimated by counting the number of days between randomization to the time of the last mental health service received as defined by the RAISE-ETP report. The *Service Utilization and Resources Form for Schizophrenia (SURF)* [27] will be used to record users’ utilization of psychiatric and psychosocial rehabilitation services by conducting telephone contacts on a three-monthly basis. Range: from 0 to 365 days over a 12-month period; from 0 to 730 days over a 24-month period.	Every 3 months	15 min

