For estimating total health care costs, we will rely on both administrative data on expenditures for implementing and delivering OTCH, and interview data, collected every three months from participants on their use of services other than OTCH. Research assistants will document service use using the Service Use and Resource Form (Table 4) every three months, during the first year, to assure adequate recall [27, 32–39].

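### Aim 3 costs OTCH from expenditure records but usual care from participant interview, and the interview form has two conflicting scopes, one of which would leave out contacts needed for retention

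*Protocol article*

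**What the plan says.** Aim 3 under Research objectives is to "Estimate the cost of delivering OTCH vs Usual FEP care over a 24-month period", and the Background adds that total and incremental costs will be estimated.

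The cost paragraph under Data collection, For the trial, names two sources. One is "administrative data on expenditures for implementing and delivering OTCH". The other is "interview data, collected every three months from participants on their use of services other than OTCH". It then identifies the instrument: "Research assistants will document service use using the Service Use and Resource Form (Table 4) every three months, during the first year".

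In Table 4 that form (SURF) sits in the retention row. Retention is obtained by "counting the number of days between randomization to the time of the last mental health service received", and the form "will be used to record users’ utilization of psychiatric and psychosocial rehabilitation services by conducting telephone contacts on a three-monthly basis". This row excludes nothing and makes no distinction between arms. Retention is one of the three service outcomes, which the article lists among its primary outcomes.

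The OTCH section under Interventions states: "Participants should not receive other concomitant psychiatric treatment during the time that they are receiving care from the OTCH team".

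**The concern.** Two matters arise from the cost paragraph.

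**Cost.** A between-arm cost difference is interpretable only if the same kind of care is measured in the same way in both arms. Here the first-episode care given by the OTCH team comes from expenditure records, while the first-episode care given by a usual-care clinic is, by elimination, part of what participants report by interview. Any under- or over-reporting in the interview then falls on the control arm's main cost item and not on its counterpart in the OTCH arm.

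**Scope of the form.** One quarterly call is described in two ways: as covering services other than OTCH (cost paragraph), and as covering psychiatric and psychosocial rehabilitation services without exception (Table 4). One interview script cannot follow both. If it followed the narrower description, the contacts that define retention for engaged OTCH participants would not be recorded.

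Both matters concern data collection. Contacts that were never recorded cannot be recovered by a later analysis, and the article states that recruitment is under way.

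**Working it through.** The plan gives no figure on this point to reproduce. The check sets the passages side by side, with one illustrative calculation for cost.

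**1. Is it the same form?** The cost paragraph refers to the Service Use and Resource Form and points to Table 4. The only such form in Table 4 is SURF, in the retention row. Both places cite the same reference [27] and the same three-monthly interval. It is one instrument.

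**2. Do the scopes agree?**

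| Place | Purpose | Stated scope |
|---|---|---|
| Cost paragraph, For the trial | Total health care costs | Interview on services other than OTCH |
| Table 4, retention row | Date of last mental health service | Psychiatric and psychosocial rehabilitation services, no exclusion |

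They do not agree. The Table 4 scope contains the OTCH contacts; the scope in the cost paragraph leaves them out.

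**3. What would follow for retention if a script used the narrower scope?** OTCH contacts would not be entered. Because the OTCH section expects no other psychiatric treatment while a participant is with the team, little else might be entered. Recorded retention could then approach 0 days for someone who in fact stayed 365 days (12-month range) or 730 days (24-month range). In usual care, clinic visits would still be entered. This is a worst case, conditional on the script, and not what Table 4 prescribes. The ten ad-hoc questions on service receipt in Table 4 would not repair it: they are asked at baseline, 12 and 24 months and are described as covering receipt of services, not the date of the last one.

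**4. What follows for cost?** Let

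- O = true cost of OTCH, taken as fully captured by administrative data
- U = true cost of usual FEP care
- c = share of usual-care cost captured by interview
- other services: the same in both arms and captured equally, so they cancel

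True incremental cost = O − U. Estimated incremental cost = O − cU. Error = (O − cU) − (O − U) = (1 − c) × U.

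The documents give neither costs nor capture rates, so c is an assumption:

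| c | Overstatement of incremental cost, as % of U |
|---|---|
| 1.00 | 0% |
| 0.90 | 10% |
| 0.80 | 20% |
| 0.70 | 30% |

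If participants over-reported (c above 1), the sign would reverse. The result shows how the error behaves, not how large it is in this trial.

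**The case against.** The strongest reply concerns retention. A reader might infer that retention is measured by different methods in the two arms. The documents do not support that. Table 4 gives one definition and one form for all participants, OTCH contacts are mental health services on any reading, and the row that defines an outcome should govern it. The restriction appears only in a sentence about costs, where leaving OTCH out of the interview component is an ordinary way to avoid counting it twice. The next sentence speaks of documenting service use without restriction. This reply stands. What remains is that one form carries two stated scopes, and the article does not say that the narrower one applies to costing alone.

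A reader might also infer that participants could not tell OTCH visits from other clinic visits. Nothing in the article says so, and several features point the other way: an orientation session with an assigned clinician, introduction to all team members, and a separate consent form for intervention clinics.

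On cost, it can be said that the article is condensed. It has no analysis section for Aim 3, and allocation rules, unit costs and valuation may well be set out in a full protocol or analysis plan that is not shown. That is fair, and their absence is no fault. It does not dispose of the point, because the article states its data sources, and those stated sources differ by arm. The 10% to 30% range remains an illustration and not a demonstrated bias.

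**Conclusion.** The point holds in a limited form.

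- **Cost:** as written, first-episode care is costed from administrative expenditure in the OTCH arm and from participant interview in the usual-care arm. The incremental cost therefore mixes programme effect with measurement method. The error is (1 − c) times true usual-care cost, assuming full capture of OTCH and other services that cancel between arms. Its size cannot be determined from the documents and is zero at full capture.
- **Retention:** the two descriptions of the form conflict. Table 4 can be read as governing, and then retention is measured alike in both arms. Harm arises only if the interview script follows the cost paragraph, in which case OTCH contacts would be missed in one arm, to the disadvantage of OTCH. It would be wrong to conclude that the plan already mismeasures retention.

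This is a cheap improvement, best made while data are still being collected.

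**What to change.** 1. Reword the cost paragraph so that SURF records all mental health contacts in both arms, OTCH team contacts included, each with its date.
2. Take retention in both arms from that common record, as Table 4 already defines it.
3. For Aim 3, measure and value clinic contacts in the same way in both arms. Use administrative expenditure for the items that OTCH adds, such as training and start-up, and state that OTCH contacts are not also counted through that expenditure.
4. Keep the costing of OTCH wholly from administrative expenditure as a sensitivity analysis.

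The three-monthly call already exists, so the cost is a change of wording, a small change to the interview script and a slightly longer call for OTCH participants. The sentence to be reworded also limits the form to the first year, whereas retention and cost run to 24 months. That is a separate matter and carries no weight here, but it can be settled in the same edit.

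### The service-use form is limited to year one in the costing text but runs every three months without limit in Table 4, while the 24-month retention outcome and cost aim need year-two data

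*Protocol article*

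**What the plan says.** Three statements in Data collection, For the trial, bear on when service use is recorded.

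- **Costing paragraph.** Total health care cost draws on "administrative data on expenditures for implementing and delivering OTCH, and interview data". The interview data are described as "collected every three months from participants on their use of services other than OTCH", with no end date. The next sentence says that research assistants complete the form "every three months, during the first year, to assure adequate recall", and it refers the reader to Table 4.
- **Table 4, Retention row.** SURF records service use "by conducting telephone contacts on a three-monthly basis". The timing column gives every three months, with no first-year limit. Retention is obtained by "counting the number of days between randomization to the time of the last mental health service received", with a range of 0 to 365 days over 12 months and "from 0 to 730 days over a 24-month period".
- **Opening sentence of the section.** All instruments are given at baseline, 12 and 24 months.

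Two other places depend on the answer. Aim 3 under Research objectives is to "Estimate the cost of delivering OTCH vs Usual FEP care over a 24-month period". The Aim 1a and Aim 1b analyses compare the arms on the service outcomes, retention among them, at both 12 and 24 months. The Abstract and Background list retention among the primary outcomes.

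**The concern.** The form that supplies both retention and non-OTCH service use has a two-year schedule in one place and a one-year schedule in another. The two purposes it serves both run to 24 months.

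The costing paragraph also gives its reason for short intervals, which is recall. If quarterly contact ends at month 12, any service use recorded for year two would have to come from a longer look-back, and the paragraph's own reasoning speaks against that.

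At stake are one of the six Aim 1 outcomes at one of its two stated test times, and the second year of Aim 3. An analysis plan written later can choose a model, but it cannot recover contacts that were never made.

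**Working it through.** **Same form?** The names differ slightly between the costing paragraph and Table 4, but the paragraph cites Table 4 and both carry the same reference number (27). I treat them as one form.

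**Inputs.** Interval of 3 months (Table 4 and costing paragraph); first-year limit (costing paragraph only); horizon of 24 months (Aim 3, and the Aim 1a and 1b analyses); retention maxima of 365 and 730 days (Table 4); 15 minutes per contact (Table 4); 300 participants (Study design).

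**Reproducing the plan's own figure.** 2 × 365 = 730 days, so the stated retention range does assume follow-up of service dates over the full 24 months.

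**Contacts under each schedule.**
- Table 4 as written: 24 / 3 = 8 contacts.
- Costing paragraph as written: 12 / 3 = 4 contacts.
- Difference: 8 − 4 = 4 contacts per participant, all in year two.

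**What each reading of year two gives** (month 12 taken as day 365, as Table 4's ranges do).

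| Reading | Year-two retention | Year-two service use for cost |
|---|---|---|
| Form stops at month 12 | No service date observed after day 365; a person still in care at month 12 cannot score higher | No interview data for 24 − 12 = 12 of the 24 months |
| Quarterly to month 12, then once at month 24 (opening sentence) | A last-service date could be asked for | A year of use from one 12-month recall, four times the 3-month interval chosen to protect recall |
| Less often in year two | Possible, but no interval is given | Same |
| Quarterly to month 24 (Table 4) | Observable over 0 to 730 days | Observable over 24 months |

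Only the last row serves both 24-month purposes without conflicting with the recall rationale, and it is the one that the first-year clause excludes.

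**Other sources.** The only other cost source named is "administrative data on expenditures for implementing and delivering OTCH". As described, it does not cover use of services outside OTCH, so it does not fill the year-two gap.

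**Cost of making the year-two calls.** 4 × 15 min = 60 min per participant; 300 × 1 h = 300 hours. This is an upper figure, because it assumes that nobody drops out and that none of these calls is already running.

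**The case against.** The strongest reply is that the first-year clause is a drafting slip. Table 4 has no such limit, the sentence just before the clause gives quarterly interviews with no end date, and both Aim 3 and the 24-month tests presuppose year-two data. One clause stands against all of these. The opening sentence on baseline, 12 and 24 months is also plainly loose, since Table 4 itself departs from it for fidelity (6, 12 and 24 months) and for retention. This largely stands as an account of what was probably intended. It does not remove the conflict: staff who work from the costing paragraph would stop calling at month 12.

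Three stronger readings are tempting, and the article does not support them.

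- *A reader might infer that year-two data are already being lost,* because recruitment began in March 2021. Nothing shown says which schedule the sites follow, so loss is possible but not established.
- *A reader might infer that half of the retention data would be missing,* since 365 / 730 = 50%. That is a share of the calendar window. Retention is one last-service date per person, not a sum over days, and such a date might be obtained at the month-24 assessment. The recall rationale is given for documenting service use; it does not show that a last-service date cannot be recalled.
- *A reader might infer that the arms are costed by different methods,* with records for OTCH and recall for usual care. The article names its sources in two sentences and has no costing section. It does not say how usual-care contacts are obtained or valued, and a condensed article commonly leaves that to a fuller document. It also does not say whether usual-care clinics hold separable expenditure records.

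**Conclusion.** The point holds as an internal contradiction about when the service-use form is collected. If the costing paragraph is followed, four of eight quarterly contacts per participant do not occur, and the 24-month retention test and the second 12 months of Aim 3 have either no service-use data or a single 12-month recall. If Table 4 is followed, nothing is lost and only the wording is wrong.

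This rests on two assumptions: that both places describe the same form, and that no year-two source exists beyond those the article names. The contradiction itself is certain; the loss is conditional. It should be settled while year-two contacts can still be made, because it affects a primary outcome at a stated test time and a whole aim, and the correction is cheap.

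**What to change.** 1. Confirm which schedule the sites are using.
2. In the costing paragraph, delete the first-year limit and state that SURF is collected every three months to month 24 in both arms, as Table 4 already schedules.
3. Amend the opening sentence of the section so that SURF is exempt from the baseline, 12 and 24-month rule.
4. If year-two calls cannot be made, name another year-two source that covers both arms, or restrict the retention and cost claims to 12 months.

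The cost is a wording change, plus at most four 15-minute calls per participant in year two (about 300 hours for 300 participants) if these are not already running.

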#### For the qualitative assessments

We will use qualitative methods to identify and characterize potential barriers/facilitators and processes that may inform the implementation of OTCH and its continuous adaptation process. In particular, we will explore factors at multiple levels (system-, organizational-, provider- and client/family member-level) by conducting semi-structured, on-line qualitative interviews with policy makers, director/health managers, and providers and focus groups or qualitative interviews with users and family members.

Qualitative interviews and focus groups will be conducted when OTCH teams begin enrollment activities and at 6- and 18-month post-randomization at all OTCH sites and at five sites randomized to usual care. We will conduct these interviews and focus groups via telephone/teleconferences. All interviews and focus groups will be audio recorded with participant’s informed consent. We will employ a purposive sampling approach to identify and invite key informants representing each group of participants [16–18].

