**Trial status:**

The OTCH trial is currently recruiting participants. Recruitment started on March 1, 2021, and is expected to be completed by December 1, 2022. This is the first version of this protocol (5/12/2021).

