### Adaptation process

As noted previously, we will use the Dynamic Adaptation Process (DAP) to adapt and implement OTCH, examine fidelity, and document barriers and facilitators. The implementation of OTCH will include four phases: Preparation, Adaptation, Implementation, and Evaluation (Fig. 2). Ongoing experience will iteratively inform adaptation as needed. We will convene multiple stakeholders (e.g., policy makers, providers, clients) in qualitative interviews and focus groups to discuss contextual conditions and identify potential modifications to the OTCH model and training curriculum. Then, once OTCH teams are established, a centralized training team will provide ongoing training using a virtual learning platform which will facilitate synchronous and asynchronous learning opportunities including virtual meetings, treatment manuals, tools, videos and other resources to support implementation. We will use mixed methods to examine to examine the implementation of OTHC to identify facilitators and barriers throughout the trial and to capture adaptation through the trials. In line with the Dynamic Adaptation Process, the qualitative data collected during the preparation phase will be presented and discussed with the OTCH clinical team as they are establishing their implementation to determine areas for adaptation via consensus. As the teams are implementing the OTCH model, the research team will use the DAP to allow us to systematically evaluate modifications made and ascertain their impact. Our approach captures processes for modification including reasons for the modification, what was modified, level of modification, and timing across phases of treatment. We also continue to examine the implementation and adaptations carried forth through OTCH teams during the 6 and 18-month qualitative data collection activities.

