### Randomization

The 21 participating clinics will first be divided into two groups based on the poverty level of the catchment area and expected enrollment of individuals with FEP for each clinic. The largest site will be matched with two clinics of a similar poverty level and clinic size as well, as noted above. The matching will be done based on a visual inspection of a scatter plot of expected enrollment by the income of each site. Then, blocks of size 2, and one block of size 3, will be randomly generated. Randomization will be performed using a randomization scheme generated by SAS 9.4. This procedure will entail (1) generating a random number 0 or 1 ten times, and (2) assigning 0 to the Usual FEP care clinic and 1 to the OTCH clinic in each matched pair. For the block of size 3, two sites will be assigned to either OTCH or Usual FEP care, and the remaining site to either OTCH or Usual FEP care as well. The statistician will notify the contact-PI once the randomization is done, and he will then call the CMHC Director to inform him/her of the assigned treatment status, followed by a written note to the Director with the same information. The random allocation within blocks of two will enable us to bring into the study one OTCH and one Usual FEP Care CMHC per month. We note that the randomization (and notification) will be done at the start of the project, which will enable us to select equal numbers of OTCH and Usual FEP Care CMHCs for data collection (at organizational, provider, and participant level) during the preparatory phase.

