Phase 1: Engagement and needs assessment (Months: 1–3)	Phase 2: Ongoing intervention and monitoring (Months: 3–18)	Phase 3: Transition (Months: 18–24)
Activities: • Introduction to all team members • Description of OTCH program • Intake assessment • Needs assessment (e.g., housing, income, etc.) • Risk and trauma assessment • Building rapport and getting to know the participant and their support network • Identification of individual goals (e.g., employment, education, relationships) • Introduction of shared decision making • Deciding on level and type of family involvement • Development of a treatment plan	Activities: • Delivery of core psychoeducation sessions • Delivery of psychosocial interventions to help achieve goals and build resiliency (e.g., social skills training, CBTp, substance use treatment, illness self-management, coping skills, and behavioral activation) • Suicide prevention • Review and revise treatment plan • Actively pursue work and school goals • Delivery of psychoeducation and support to family • Relapse prevention • Explore transition readiness	Activities: • Determine gains made and goals attained • Decrease frequency of services delivered • Develop a transition plan • Identify and connect to mental health services in the community • Identify and connect to community-based supports • Engage family in transition plan and identify their role • If possible, test whether these new services align with participant’s preferences

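### The 6- and 18-month qualitative waves are counted from a single clinic randomization at project start, so read literally the 6-month wave falls before OTCH begins at 3 or more of the 10 monthly OTCH clinic entries

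*Protocol article*

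**What the plan says.** The section on qualitative assessments uses two clocks. For the first wave it says: "Qualitative interviews and focus groups will be conducted when OTCH teams begin enrollment activities". The two later waves are held "at 6- and 18-month post-randomization at all OTCH sites and at five sites randomized to usual care".

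The Randomization section describes one clinic-level allocation: "the randomization (and notification) will be done at the start of the project". It places this ahead of data collection in a preparatory phase. On the block structure it says that "blocks of size 2, and one block of size 3, will be randomly generated", and that pairing will make it possible to "bring into the study one OTCH and one Usual FEP Care CMHC per month".

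The Adaptation process section gives the purpose of the later waves: to go on examining implementation and the "adaptations carried forth through OTCH teams during the 6 and 18-month qualitative data collection activities". Table 3 describes a 3-month initial training that comes before OTCH is implemented. Table 2 gives the last stage of the programme as "Phase 3: Transition (Months: 18–24". Trial status reports: "Recruitment started on March 1, 2021, and is expected to be completed by December 1, 2022".

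**The concern.** The follow-up waves are meant to show what OTCH teams are doing and how they are changing the model. That requires teams that are already delivering OTCH. If all clinics are randomized on one date but start one after another over many months, a wave fixed at 6 months after that date reaches some clinics with half a year of experience and others that have not begun. At the latter the nominal follow-up interview would come before the nominal baseline interview. The material gathered there could not serve the stated purpose, and the 6-month label would not describe how long a team had been working.

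The stakes are limited to the qualitative component. It is nevertheless part of how a hybrid trial learns about implementation, and the mistiming follows from a rule that the article states.

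**Working it through.** **Inputs**
- Clinics: 21, in one block of 3 and otherwise blocks of 2 (Randomization).
- Random draws: 10 (Randomization).
- Pace: one OTCH clinic entry per month (Randomization).
- Follow-up waves: months 6 and 18 after randomization (qualitative assessments).
- Lag L, in months, from randomization to the first clinic's OTCH start: not stated, so varied.

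**Reproducing the plan's figure.** Blocks = (21 − 3)/2 + 1 = 9 + 1 = 10. This agrees with the ten draws and gives 10 monthly entries, k = 0 to 9.

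**Start of OTCH at entry k** = L + k months after randomization.

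**Entries not yet started at the 6-month wave** = the number of k with L + k > 6, which for L of 0 or more is the smaller of 10 and 3 + L.

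**Time in operation at a wave held at month w** = w − L − k. A negative value means that OTCH has not begun.

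| L (months) | Entries after the 6-month wave | Operation at month 6, first to last clinic | Operation at month 18, first to last clinic |
|---|---|---|---|
| 0 | 3 of 10 | +6 to −3 | 18 to 9 |
| 1 | 4 of 10 | +5 to −4 | 17 to 8 |
| 3 | 6 of 10 | +3 to −6 | 15 to 6 |
| 6 | 9 of 10 | 0 to −9 | 12 to 3 |
| 7 | 10 of 10 | −1 to −10 | 11 to 2 |

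L = 0 is the most favourable case: entries at months 7, 8 and 9 still fall after the wave. L = 3 is what results if the 3-month training begins at randomization and the first clinic starts when it ends; the article does not say when training begins relative to randomization.

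The table counts monthly entries. If the block of three supplies two OTCH clinics and enters late, the number of clinics affected is one higher.

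**After re-anchoring.** With both waves counted from each clinic's own start, time in operation is 6 months at every clinic at the first follow-up, and no clinic is unstarted. At the 18-month wave the longest-enrolled participant is at month 18 exactly, the first day of the tabulated transition phase.

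**The case against.** The strongest reply is that the wording is loose and the design is sound. The retention row of Table 4 counts days from randomization with ranges of 0–365 and 0–730, which fits a participant's own day 0 and not one date for all clinics. The stated purpose in the Adaptation process section presupposes working teams. On that reading the waves are 6 and 18 months after a clinic starts, and the mistiming disappears. The article is also a condensed account, and a site-level interview calendar may sit in the full protocol. This has force, and it is why the point is one of reconciliation. It does not remove the point: the only randomization the article defines is the single clinic-level one, and the qualitative section names randomization as its anchor immediately after using a different anchor for the first wave.

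It is also fair that the monthly pace is described as something the design makes possible, not as a fixed schedule, and that neither the randomization date nor the length of the preparatory phase is given. The counts are therefore a range.

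A reader might go further in three ways that the article does not support.
- **That the study can learn nothing about transition and discharge.** Fidelity is assessed at 24 months using provider feedback, supervision calls and site visits. Provider and participant measures are also taken then, and Study management provides for ongoing qualitative interviews. Since the final phase is defined as starting six months before discharge, a participant discharged early could also reach it sooner.
- **That the waves fell before the first participant was enrolled.** This needs randomization to be dated near trial registration in January 2020, which the article does not say.
- **That comparisons between waves and clinics are confounded by calendar time.** No such comparison is planned. Sampling is purposive, and the stated aim is to inform implementation and continuing adaptation.

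**Conclusion.** The point holds as an inconsistency in timing. Taken literally, the qualitative section and the Randomization section put the 6-month wave before OTCH begins at 3 or more of the 10 monthly OTCH entries: 3 with no lag, 6 with a 3-month lag, all 10 from 7 months. This assumes one entry per month over 10 blocks and that the first wave is held clinic by clinic. If the first wave were instead one common date, the order would not reverse, but the late clinics would still have no OTCH delivery to describe at month 6.

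One limitation should be stated but does not call for correction. A wave at month 18, even when counted from clinic start, reaches at most the opening day of the transition phase in Table 2, so that phase is covered mainly by the 24-month fidelity and outcome measures. A wave at about 24 months in its place would delay feedback for adaptation and leave an 18-month gap after month 6 (24 − 6 = 18). That is a trade-off for the investigators.

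Outcomes, allocation, power and the 12- and 24-month comparisons are not affected.

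**What to change.** In the section on qualitative assessments, replace randomization as the anchor of the 6- and 18-month waves with each OTCH clinic's own start of enrollment, which is the clock already used for the first wave. Give each of the five usual-care clinics the start date of its matched OTCH clinic, and state in advance which date applies in the block of three if it contains two OTCH clinics. Use the same clock in the Adaptation process section. If clinic start is what was meant all along, the same edit serves as the clarification.

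The number of waves, sites and interviews does not change. The cost is a wording change and an interview calendar spread over more months, because clinics reach months 6 and 18 on different dates.
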